## Abstract

**Introduction:**

Weight gain in adulthood is a common potentially modifiable breast cancer risk factor. Intermittent 5:2 diets (two low-calorie days/week) have proven efficacy for weight loss among people with overweight or obesity and can promote sustained awareness and mindfulness of diet choice and help appetite control.

This trial aims to test whether a less intensive 6:1 intermittent diet programme (one low-calorie day/week) is a feasible intervention to promote healthy eating and prevent weight gain in women at increased risk of breast cancer.

**Methods and analysis:**

Single arm prospective feasibility trial in 30 healthy weight women aged 18–40 years, at moderate or high risk of breast cancer (≥17% lifetime risk and/or ≥3% 10 year risk at 40 years), body mass index 20–25 kg/m^2^. Participants will be entered to a 16-week 6:1 diet programme involving 1 day consuming 1000 kcal and healthy eating for 6 days a week. Participants will also be advised to meet physical activity recommendations for health (≥150 min of moderate intensity physical activity/week and resistance exercise two times per week). The programme will be supported remotely by dietitian calls at baseline, week 1, 4, 8, 12 and 16. Participants will also be provided access to a trial-specific private monitored Facebook group which includes information and the opportunity for peer support.

Co-primary outcomes are: (a) uptake to the trial, (b) retention rate, (c) adherence to the 6:1 diet and (d) participant feedback on acceptability of the programme. Secondary outcomes include characteristics of those recruited and completing the programme and a preliminary evaluation of benefits and harms. This includes changes in body weight and body composition (bioelectrical impedance), diet quality, physical activity, binge eating, sleep quality (Pittsburgh Sleep Quality Index), menstrual cycle length and potentially diet-related adverse events, that is, fatigue, constipation, dizziness, headache, indigestion. Exploratory outcomes include the impact of low-calorie days on dietary intake and physical activity across the week and any differences in adherence to the low calorie days across the menstrual cycle.

**Ethics and dissemination:**

This trial has been approved by South Central—Berkshire B Research Ethics committee (rec reference 24/SC/0321). Findings will be disseminated via peer-reviewed journals, national and international cancer prevention and obesity conferences and cancer prevention charitable bodies.

**Trial registration number:**

ISRCTN14330469.

STRENGTHS AND LIMITATIONS OF THIS STUDYThe trial has clear progression criterion to decide whether to advance to a randomised controlled efficacy trial.This feasibility trial is not powered or of sufficient duration to demonstrate changes in weight or diet or physical activity behaviours.Women joining this trial are likely to be highly motivated and adherence may not reflect that seen in the wider population.The trial includes a quantitative evaluation but does not include a qualitative evaluation of acceptability of the programme.

## Introduction

 Adult weight gain is a potentially modifiable risk factor for developing breast cancer as well as nine other weight-related cancers in women.^1^ In the UK, 35% of women are a healthy weight with 62% overweight or obese.^2^ On average, women in the UK gain 10 kg of weight during adult life, mostly between the age of 18 and 40 years.^3^ This level of weight gain increases weight-related cancers in women by 20%, specifically increased rates of breast (15%), endometrium (50%) and kidney cancer (30%).^1^

Weight gain is a consequence of habitual chronic positive energy balance, largely driven by excess energy intake and often high fat, high sugar diets.^3^ Once weight is gained, it is difficult to lose and keep off for both physiological and behavioural reasons.^4^ Weight gain is common among women attending family history clinics (FHCs) who are at increased genetic risk of breast cancer. Weight gain has an equal or greater effect on the relative risk for breast cancer among women with a family history of breast cancer compared with those without a family history.^5^ Thus, there is an unmet need for effective diet and physical activity interventions to prevent weight gain and manage breast cancer risk in this population.

Our previous research has demonstrated that the 5:2 diet, involving 2 days in the week with restricted energy intake (800–1000 kcal/day), is efficacious for weight loss in people with overweight or obesity,^6^ and this approach has been successfully implemented in many healthcare settings in the UK and worldwide including patients with cancer^7^ and type 2 diabetes.^8^ Our research has shown that intermittent diets (such as the 5:2 diet) can promote sustained awareness and mindfulness of diet choice and helps to control appetite, which in turn promote maintained lower energy intakes across the week.^9^ It is likely that the intensity of dietary restriction needed for the prevention of weight gain is less than that needed to induce weight loss. The present trial will therefore test whether a less intensive 6:1 intermittent diet including one low-calorie day/week is acceptable and has the potential to promote a healthy diet to prevent weight gain in women at increased risk of breast cancer who are a healthy weight.

The trial will also assess if the diet could be associated with any harms. We will assess the effects of the diet on disordered eating. Intermittent weight loss diets have mainly demonstrated improvements in eating patterns in the weight loss setting,^10 11^ but some concerns have been expressed of increased eating related thoughts, hunger and fear of loss of control among healthy-weight individuals consuming such diets.^12 13^ There is also evidence that reduced calorie intakes may be associated with reduced physical activity and reduced energy expenditure, in order to conserve energy, with potential detrimental effects on lean body mass.^14^ Some people following energy restricted diets report poorer sleep quality,^15^ although findings are not consistent.^16^ The planned trial therefore includes assessments of dietary intake, an objective measure of physical activity (ACTi graph),^17^ sleep quality (Pittsburgh Sleep Quality Index (PSQI)) and body composition (bioelectrical impedance, Tanita MC980MA), waist, hip circumferences to obtain preliminary data of these effects.

As there is a potentially bi-directional relationship between low-calorie diets and menstrual cycle in young women, we will ask participants to record the first day of their menstrual cycle throughout the trial. This is being done for completeness as we do not anticipate the modest energy restriction with the 6:1 intermittent diet will directly affect menstrual cycle function which can occur with longer spells of low-calorie intake.^18^ Inclusion of menstrual cycle dates will also provide preliminary data of any potential differences in dietary adherence across the menstrual cycle and whether adherence is reduced in the premenstrual weeks when women often report increased appetite and carbohydrate craving.^19^

In line with guidance on best practice in evaluating complex interventions, it is important to test the acceptability and any potential benefits and harms of this novel diet in a feasibility trial, as well as assess the major uncertainties in conducting an efficacy trial of this diet.^20^ The evaluation of acceptability, adherence and exploratory evaluation of weight and health behaviours and patient experience in the trial will determine whether we should proceed to a larger efficacy trial.

### Aim

To test whether a 6:1 intermittent diet programme (one low-calorie day/week) is an acceptable intervention and has the potential to promote healthy eating and prevent weight gain in women at increased risk of breast cancer.

## Methods and analysis

### Trial design

This trial is a single arm prospective feasibility trial among women aged 18–40 years, at moderate or high risk of breast cancer (>17% lifetime risk and/or with 10-year risk of breast cancer of >3% at age 40 years)^21^ with a body mass index (BMI) ≥20 and ≤25 kg/m^2^.

### Trial setting and recruitment

Participants will be identified from the regional FHC and the Cancer Genetics Clinics at Manchester University NHS Foundation Trust (MFT). Recruitment will be through direct invitation by members of the clinical teams, mailing the patient information sheet and promotion via the Prevent Breast Cancer charity website and related social media platforms such as Facebook and X. These women will have their attendance at the FHC and genetics clinics verified by a member of the relevant teams. The planned trial start and end dates are 17 March 2025 and 17 March 2026. All trial face-to-face assessments will be undertaken by the research team in a research facility at the main recruiting site at Wythenshawe Hospital. All participants will have a trial run-in week before they receive baseline diet advice when we ask them to record 7 days of habitual diet and wear an activity monitor to assess their habitual diet and physical activity patterns.

Box 1Inclusion and exclusion criteria for the Prevent 6:1 trialInclusion criteriaAged 18–40 years.Born female and not undergone gender reassignment X.Moderate or high risk of breast cancer (≥17% lifetime risk or with 10-year risk of breast cancer of ≥3% at 40)^21^ and have attended/currently attending NHS family history/genetics clinic.BMI 20–25 kg/m^2^.Able to communicate (written and spoken) in English or any other language and access to a phone as we have access to an interpreter service.Able to attend two face-to-face appointments at MFT at baseline and week 16.Not pregnant or planning to become pregnant in the next 16 weeks. Where appropriate, participants will need to have negative urine pregnancy test at screening and agreement to maintain contraception or abstinence during the trial.Exclusion criteriaPrevious breast cancer or bilateral preventative mastectomy.Currently trying to gain weight.Previously had weight loss surgery or taking weight loss medication.Have a medical condition that influences diet and weight, for example, diabetes, inflammatory bowel disease or cystic fibrosis.Current diagnosis of a psychiatric disorder, that is, bipolar psychotic disorder or current self-harm.Current or previous diagnosis of an eating disorder.Substance abuse or harmful alcohol use as indicated by a score of 16 or above on the AUDIT Test.Severe binge eating assessed by a score of 27 or more on the BES.Severe depression assessed by a score of 15 or more on the PHQ-9.Severe anxiety assessed by a score of 15 or more on the GAD-7 questionnaire.Confirmed pregnancy via a pregnancy test, planning pregnancy in the next 16 weeks, or currently breastfeeding.AUDIT, Alcohol Use Disorders Identification Test; BES, Binge Eating Scale30; BMI, body mass index; GAD-7=General Anxiety Disorder-7; MFT, Manchester University Foundation Trust; PHQ-9, Patient Health Questionnaire-9. NHS, National Heath Service.

### Sample size

We plan to recruit 30 participants which provides an acceptable degree of precision for estimates for the three co-primary outcomes of the trial: uptake, retention and dietary adherence. Using a 90% CI, a sample size of 30 provides estimates of trial uptake of 10% with an error of ±9%, trial retention at 16 weeks of 50% with an error of ±15% and adherence to the 6:1 intermittent diet (ie, the number of weeks which included one low calorie/day versus the number of weeks on the trial 40% with an error of ±15%.

Previous diet studies in this population have had an uptake of around 15%.^25^ To recruit 30 women, we predict we will need to invite ~200 women. There are currently ~2000 women aged 18–40, with BMI 20–25 kg/m^2^ within the regional FHC at MFT. We anticipate recruitment will take place over 12–20 weeks.

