### Outcomes

#### Co-primary feasibility outcomes

Uptake rate as a percentage of the number of eligible participants invited who consent to take part for the trial.Retention rate measured as the number of consented participants who complete the 16-week trial.Self-reported adherence to the 6:1 programme across the 16-week trial.Patient acceptability of the 6:1 programme using a validated intervention evaluation questionnaire at the end of the programme or at time of withdrawal from the trial.^28^

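### The ±9% precision for uptake is computed on the 30 recruits, but uptake is measured among women invited; the half-width is about two to three times too wide, in the conservative direction

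*Protocol article*

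**What the plan says.** The Sample size section of the protocol article justifies the target of 30 by precision: "We plan to recruit 30 participants which provides an acceptable degree of precision for estimates for the three co-primary outcomes of the trial", namely uptake, retention and adherence. It then gives one half-width for each at the 90% level. For uptake: "a sample size of 30 provides estimates of trial uptake of 10% with an error of ±9" points. For retention: "trial retention at 16 weeks of 50% with an error of ±15" points. For adherence it gives 40%, also with ±15 points.

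Under Co-primary feasibility outcomes, uptake is defined as follows: "Uptake rate as a percentage of the number of eligible participants invited who consent to take part for the trial".

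The second paragraph of the Sample size section cites an uptake of around 15% in previous diet studies and concludes: "To recruit 30 women, we predict we will need to invite ~200 women". Table 3 makes uptake a progression criterion: green above 15%, amber from 10% to 15%, red below 10%.

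**The concern.** A proportion's precision depends on its denominator. Retention and adherence are assessed in the women who join, so 30 is a reasonable denominator for them. Uptake is assessed in the women approached, and the 30 who join are the count on top. Read literally, 10% uptake in a sample of 30 means three consenting women, which cannot describe a trial that recruits 30.

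As written, the precision claimed for a co-primary outcome does not belong to the outcome as defined. Someone relying on the Sample size section would take the uptake interval to be 1% to 19%, much wider than the design will deliver, and could carry the same denominator into the analysis or into planning of the efficacy trial.

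**Working it through.** **Inputs**

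- Confidence level 90%, so z = 1.645 (Sample size).
- Target recruits: 30 (Sample size).
- Rates in the precision statement: uptake 10%, retention 50%, adherence 40% (Sample size).
- Uptake in previous studies about 15%; about 200 women to be invited (Sample size).
- Uptake denominator: eligible women invited (Co-primary feasibility outcomes).
- 300 invited: not stated. It follows from 30 recruits at 10% uptake, 30 / 0.10 = 300.

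**Step 1: reproduce the stated figures.** Wald half-width = z × √(p(1 − p)/n), with n = 30:

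- Uptake: 1.645 × √(0.10 × 0.90 / 30) = 9.0 points (stated 9).
- Retention: 1.645 × √(0.50 × 0.50 / 30) = 15.0 points (stated 15).
- Adherence: 1.645 × √(0.40 × 0.60 / 30) = 14.7 points (stated 15).

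All three reproduce. Solving the uptake formula for n at p = 0.10 and ±9 points gives n = 1.645² × 0.09 / 0.09² ≈ 30.1, so the denominator used was 30. A 95% interval at n = 30 would give ±10.7 points, which does not match.

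**Step 2: use the defined denominator.**

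| Uptake | Women invited | Consenting | 90% half-width | Interval | Step 1 figure (9.01) ÷ this |
|---|---|---|---|---|---|
| 15% | 200 (stated) | 30 | 1.645 × √(0.15 × 0.85 / 200) = 4.15 points | 10.8% to 19.2% | 2.2 |
| 10% | 200 (stated) | 20 | 1.645 × √(0.10 × 0.90 / 200) = 3.49 points | 6.5% to 13.5% | 2.6 |
| 10% | 300 (derived) | 30 | 1.645 × √(0.10 × 0.90 / 300) = 2.85 points | 7.2% to 12.8% | 3.2 |

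**Step 3: check that the formula does not drive the result.** Wilson 90% intervals are 11.3% to 19.6% for 30/200, 7.0% to 14.0% for 20/200 and 7.5% to 13.2% for 30/300. Their half-widths are 4.2, 3.5 and 2.9 points. For 3/30 the Wilson half-width is 9.2 points. The gap is due to the denominator, not to the choice of interval.

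**Step 4: could another reading of the denominator rescue ±9?** If 30 women consent, uptake p forces a denominator of 30/p. A denominator of 30 would then mean 100% uptake, and 10% uptake means 300 women. If the eligible women invited are somewhat fewer than all those approached, the half-width changes somewhat, but no count consistent with 30 recruits at 10% uptake gives a denominator of 30.

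**The case against.** The strongest reply is that nothing in the design turns on this. The error is conservative. The conclusion that 30 recruits give acceptable precision holds for uptake more comfortably than claimed, and the retention and adherence figures are right. That stands, and it limits how serious the point is.

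A reader might go further in three directions that the article does not support.

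- **That uptake cannot be classified for progression.** The stated 1% to 19% does cover all three colours. But Table 3 sets cut-offs for percentages and nothing in the article applies a confidence interval to them, so the ±9 does not alter a progression decision. Nor does the correction settle the colour: 7.2% to 12.8% still spans red and amber, and 10.8% to 19.2% still spans amber and green.
- **That 10% and 15% contradict each other.** The 10% serves the precision statement and equals the red/amber boundary in Table 3, just as the 50% for retention does. The 15% is past experience used to plan invitations. Precision may be quoted at a threshold value. At 10%, 200 invitations would yield 20 women, but the article reports a pool of about 2000, so more could be invited.
- **That uptake will be inflated by self-referral or by unknown eligibility.** Recruitment also uses "promotion via the Prevent Breast Cancer charity website and related social media platforms such as Facebook and X". The definition already restricts uptake to eligible women invited, and nothing says that women who come forward by themselves enter the numerator. Counting rules by recruitment source are commonly left to the full protocol or analysis plan, which is not shown, so their absence is no finding.

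**Conclusion.** The stated uptake precision is wrong as written. The ±9 points reproduces only with the 30 recruits as denominator, whereas the article's own definition puts eligible women invited there and its own planning expects about 200 of them. The half-width is too wide by a factor of 2.2 on the article's 15% and 200, 2.6 at 10% and 200, and 3.2 at 10% and the derived 300: roughly two to three.

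This rests on the Wald formula that reproduces the article's figures (Wilson gives nearly the same widths) and on the number of eligible women invited being near the planned figure. The sample size, the outcome definition and the Table 3 thresholds are unaffected. It is an error to correct, not one that the trial depends on.

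**What to change.** In the Sample size section, separate uptake from the other two outcomes. A possible wording: *Uptake will be estimated among eligible women invited. With about 200 invited, the 90% CI half-width is about ±4.2 percentage points at 15% uptake and ±3.5 at 10%; if 300 must be invited to reach 30 recruits at 10% uptake, it is about ±2.8. For retention (50%) and adherence (40%), 30 participants give half-widths of about ±15 points.*

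Use the same denominator when the uptake interval is reported. The cost is a sentence or two of protocol wording, with no additional participants, visits or data, and no change to the target of 30 or to Table 3.

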### The 6.1 diet programme

#### Dietary advice

Participants will receive advice on adopting an intermittent 6:1 diet which involves one 1000 kcal day/week including ~70 g of protein and ~100 g carbohydrate. The 1000 kcal diet comprises 6–7 portions ~210 g of lean protein containing foods, 3–4 portions of wholegrain carbohydrates, one 7 g portion of fat, five 80 g portions of vegetables, two portions of fruit and three portions of dairy or dairy alternatives. An example of a low-calorie day is provided in table 1. The diet also includes 6 days/week of healthy eating Mediterranean-type diet which provides approximately 30% energy from fat (15% monounsaturated fatty acids, 8% polyunsaturated fatty acids, 7% saturated fatty acids), 25% energy from protein and 45% from low glycaemic load carbohydrate. The diet includes at least five portions of vegetables and two portions of fruit/day and is limited in alcohol (<10 units, 80 g /week) as described previously.^6^ Food and drink will be self-selected and not provided by the trial team. The diet can be successfully adapted for people of different ethnicities and those following omnivorous, vegetarian and vegan diets.

**Table 1 T1:** Example of a low calorie day for a mixed omnivorous diet which includes meat, fish or dairy

	Portion	Numbers of the food portions/day					
		Dairy	Protein	Carb	Veg	Fruit	Fat
*Breakfast*
Poached egg	1 egg	0	1	0	0	0	0
Grilled tomatoes	7 cherry tomatoes	0	0	0	1	0	0
Tea/coffee	1 mug	0	0	0	0	0	0
*Midmorning*							
Natural yoghurt ½ handful of berries	150 g 40 g	1	0	0	0	1/2	0
*Lunch*							
Wholegrain bread	1 medium slice	0	0	2	0	0	0
Tuna	⅓ of a 120 g can	0	1	0	0	0	0
Green salad	Cereal bowl (80 g) with oil-free dressing	0	0	0	1	0	0
Satsuma	1	0	0	0	0	1/2	0
*Mid afternoon*							
Low fat cheese	30 g /match box size	1	0	0	0	0	0
Apple slices	I medium apple (80 g)	0	0	0	0	1	0
Tea/coffee		0	0	0	0	0	0
*Evening*							
Vegetable rice	4 tablespoons cooked rice and 160 g of mixed vegetables	0	0	2	2	0	0
Chicken curry	90 g/average chicken breast (no skin) and ½ can tomatoes, 1 dessert spoon of oil	0	3	0	1	0	1
*Bedtime*							
Low fat houmous	1 level tablespoon	0	1	0	0	0	0
Pepper sticks	½ red pepper	0	0	0	1	0	0
Milk in drinks	1 small glass (200 mL)	1	0	0	0	0	0
Total portions a day		**3 portions**	**6 portions**	**4 portions**	**5 portions**	**2** **portions**	**1 portion**

#### Physical activity advice

The programme also asks participants to meet physical activity recommendations for health (≥150 min of moderate intensity/week and resistance exercise two times per week) in line with the WHO guidelines on physical activity and sedentary behaviour.^26^ Suitability and safety to undertake an unsupervised home-based physical activity programme will be assessed using the Physical Activity Readiness questionnaire.^27^ Participation in physical activity is encouraged but is not essential for joining the trial. General practitioner clearance will be requested where required.

#### Dietetic support

Participants will receive their initial advice to follow the diet and engage in physical activity by phone or video call after completion of the 7 days of habitual diet records and ACTigraph physical activity monitoring (week 0). They will be offered dietetic support via phone or video call (MS teams) or email reviews with one of the trial dietitians at week 1, 4, 8, 12 after starting the programme and receive exit diet and physical activity advice after their 16-week review. Trial dietitians will have previous experience and/or recent training in breast cancer risk estimation, risk factors and advising intermittent diets.

Participants will also be provided with access to a trial specific private monitored Facebook group. This includes dietitian-led online group question and answer sessions, an opportunity to raise questions and have peer support chat with other women. Also updates on information on diet, the trial and risk factors for breast cancer risk. Access to the private Facebook group is by invite only to trial participants who are reminded not to post personal information. Participants who opt to use it will be advised of the data protection policy. At the end of the trial, all participants will be removed from the private Facebook group and the site will no longer be monitored.

